## Abstract

**Background:**

Although repetitive transcranial magnetic stimulation (‘TMS’) is becoming a gold standard treatment for pharmacoresistant depression, we lack neural target biomarkers for identifying who is most likely to respond to TMS and why. To address this gap in knowledge we evaluate neural targets defined by activation and functional connectivity of the dorsolateral prefrontal cortex-anchored cognitive control circuit, regions of the default mode network and attention circuit, and interactions with the subgenual anterior cingulate. We evaluate whether these targets and interactions between them change in a dose-dependent manner, whether changes in these neural targets correspond to changes in cognitive behavioral performance, and whether baseline and early change in neural target and cognitive behavioral performance predict subsequent symptom severity, suicidality, and quality of life outcomes. This study is designed as a pragmatic, mechanistic trial partnering with the National Clinical TMS Program of the Veteran’s Health Administration.

**Methods:**

Target enrollment consists of 100 veterans with pharmacoresistant Major Depressive Disorder (MDD). All veterans will receive a clinical course of TMS and will be assessed at ‘baseline’ pre-TMS commencement, ‘first week’ after initiation of TMS (targeting five sessions) and ‘post-treatment’ at the completion of TMS (targeting 30 sessions). Veterans will be assessed using functional magnetic resonance imaging (fMRI), a cognitive behavioral performance battery, and established questionnaires. Multivariate linear mixed models will be used to assess whether neural targets change with TMS as a function of dose (Aim 1), whether extent and change of neural target relates to and predicts extent of behavioral performance (Aim 3), and whether extent of neural target change predicts improvement in symptom severity, suicidality, and quality of life (Aim 3). For all three aims, we will also assess the contribution of baseline moderators such as biological sex and age.

**Discussion:**

To our knowledge, our study will be the first pragmatic, mechanistic observational trial to use fMRI imaging and cognitive-behavioral performance as biomarkers of TMS treatment response in pharmacoresistant MDD. The results of this trial will allow providers to select suitable candidates for TMS treatment and better predict treatment response by assessing circuit connectivity and cognitive-behavioral performance at baseline and during early treatment.

**Trial registration:**

ClinicalTrials.gov NCT04663481, December 5th, 2020, retrospectively registered. The first veteran was enrolled October 30th, 2020.

## Background

Major depressive disorder (MDD) is the leading cause of disability worldwide [1]. Due to a lack of mechanistically anchored quantitative tests for identifying the correct intervention for individual patients at their first presentation, treatment choice is often a years-long trial-and-error process. One reason for the unpredictability of therapeutic response is the heterogeneity of MDD, both clinically and in terms of underlying neurobiology [2]. While definitions vary, pharmacoresistant or treatment-resistant depression is defined as lack of response to at least one antidepressant trial of adequate dose and duration [3]; up to 50% of MDD patients meet these criteria [4]. Residual depressive symptoms are associated with a higher risk of recurrence, worse functioning, and increased personal and economic burden [5]. Furthermore, pharmacoresistant depression can be life threatening: 30% of patients have one or more lifetime suicide attempts, which is at least twice the rate of those with non-resistant depression [6].

Neural circuits (hereafter circuits) consist of vast numbers of interconnected neurons comprising the anatomical and functional networks of the brain [7]. Circuits involved in cognitive control are promising targets for pharmacoresistant depression. Dysfunctions in the cognitive control network and reciprocal pathways linking this circuit with attention and default mode networks (DMN) are characteristic of MDD [8] (for review [2, 7]). Depressed patients who do not remit on commonly prescribed pharmacotherapies show dorsolateral prefrontal cortex (DLPFC) hypoactivation along with hypoconnectivity between the DLPFC and anterior cingulate cortex [9]. Corresponding frontoparietal attention network hypoconnectivity is also observed in MDD [10, 11] and correlated with behavioral indices of poor attention, such as false alarm errors on cognitive testing, in related anxiety disorders [12]. Some degree of DMN dysfunction is observed in persistently unwell MDD patients [13] and can identify MDD patients who do not remit on antidepressants [14]. Reflecting the close interplay of cognitive control and attention networks, pharmacoresistant patients with MDD are also characterized by impaired connectivity of the DLPFC and precuneus component of the attention network [15]. As an interposed area involved in the interactive effects of cognitive control and other circuits, subgenual anterior cingulate cortex (sgACC) impairments are also thought to exacerbate broader circuit dysfunction in MDD (for review [10]). Pharmacoresistant MDD patients show persistent hypoactivation and connectivity involving the sgACC [16] in analyses of brain metabolism using positron emission tomography.

Repetitive transcranial magnetic stimulation (rTMS, hereafter TMS) was cleared by the U.S. Food and Drug Administration (FDA) for pharmacoresistant MDD in 2008 and has become an important treatment option in clinical settings. While the putative therapeutic mechanism of TMS remains under study, recent neuroimaging studies provide insight into brain activity changes associated with therapeutic TMS of the DLPFC. Neuroimaging studies of TMS in both healthy subjects and in MDD have focused mostly on circuits probed during resting conditions. In healthy subjects our prior work has shown that DLPFC stimulation induces an inverse correlation between resting connectivity of the DLPFC (middle frontal gyrus) and the medial frontal region of the DMN [17] as expected for flexible circuit organization. Neuroimaging studies implicate pre-stimulation baseline DLPFC-sgACC connectivity in the mechanisms of clinical action of TMS [18, 19]. In 13 patients with MDD, more intact negative (i.e., “anticorrelated”) DLPFC-sgACC resting state functional connectivity prior to DLPFC stimulation was associated with superior amelioration of clinical symptoms [18]. In a small subset of controls and two patients scanned post-TMS, individual differences in DLPFC-sgACC connectivity were highly reproducible [19]. These findings suggest that suppression of the subgenual anterior cingulate cortex via DLPFC stimulation may be an antidepressant mechanism of TMS, and that baseline connectivity is a viable imaging biomarker to optimize TMS at the individual level. When imaged after TMS, responders (*n*=5/12) showed improvement in the negative connectivity of DLPFC and sgACC, whereas non-responders (*n*=7/12) did not [20]. In a complementary study, 17 MDD patients were found to show attenuation of abnormally positive sgACC-DMN connectivity, along with reduced DLPFC to medial prefrontal connectivity, but not of the DLPFC and sgACC [21]. However, in this latter study, TMS-related connectivity changes were not associated with clinical improvement. Most recently, Weigand et al. [22] demonstrated that sgACC-DLPFC connectivity could predict clinical response to TMS; this study incorporated two datasets, inclusive of 25 participants who received unblinded TMS, and 16 participants who received sham stimulation and open-label stimulation from Taylor et al. [23]. Together, findings to date suggest that TMS selectively modulates functional connectivity both within and between the cognitive control network and interconnected regions of the frontal cortex and DMN, and that modulation of these interactions by the sgACC may play an important mechanistic role in predicting the effect of TMS on alleviating depression. The results also highlight the need for systematic investigation using imaging biomarkers in samples with greater power for statistical inference.

Drawing on this evidence, a premise of our study is that TMS of the DLPFC will have antidepressant efficacy via direct effects on cognitive control processes that contribute to regulatory functions and that involve interactions with attention and default mode networks.

Despite the wide scale adoption of TMS, we still lack mechanistically-driven biomarkers designed to identify who is most likely to respond, and why; these measures are crucial for broader adoption of TMS and are possible with near-term discoveries. In our recent multisite trial of TMS in pharmacoresistant depression [24], standard clinical measures did not predict remission [25]. While there are relatively few side effects from TMS as compared to other neuromodulation techniques, undergoing a full course of this treatment when it will ultimately not lead to remission can be discouraging for the patient and psychiatrist, prolongs suffering and is economically inefficient. For these reasons, there is an urgent need for well-powered multisite clinical trials that advance a biomarker-driven approach to identifying which patients will benefit from TMS and through which mechanisms. Furthermore, existing rubrics can be immediately used to translate observed findings into clinical practice [26]. Our findings will, more broadly, also lay important foundations for the systematic experimental manipulation of stimulation protocols and parameters in future mechanistic trials.

Our study objective is to systematically evaluate cognitive control network connectivity and behavior as response biomarkers for the effect of TMS in pharmacoresistant MDD, and the extent to which connectivity and behavior are predictive of clinical symptoms, function, and suicidality outcomes. We strive to meet this objective by exploring the following aims:

### Aim 1

To evaluate a response biomarker of the effect of TMS on promoting cognitive control. We will assess whether activation and functional connectivity of the DLPFC-anchored cognitive control network, and interactions with sgACC, attention and default mode regions involved, change in a session (akin to dose)-dependent manner. Our broad hypothesis is that functional connectivity will change from the pre-treatment baseline to reassessment early after commencement of TMS (targeting 5 sessions) and later, post- completion of treatment (targeting 30 sessions). Related, we hypothesize that the early change will be most pronounced for patients with intact connectivity at baseline; later change post-treatment will be observed for those with more impaired baseline connectivity. First, we will address the mechanistic question of whether early changes in circuit connectivity are necessary, if not sufficient, for subsequent circuit and clinical changes observed post-TMS. Second, we will systematically test whether the extent of change in connectivity is related to the extent of dysfunction at the pre-stimulation baseline. Third, we will probe whether observed changes in connectivity increase as a session-dependent function of the total number of TMS sessions. In addressing these issues, we will incorporate a methodological technique to quantify the site of DLPFC stimulation with anatomical precision.

### Aim 2

To assess whether the extent of change in a DLPFC cognitive control network connectivity response biomarker is related to corresponding change in behavioral performance. Our broad hypothesis is that the extent of connectivity change will be related to the extent of change in behavioral performance, and that this relationship will be most pronounced for patients with relatively intact connectivity at baseline; later change will be observed in patients with more impaired baseline connectivity.

### Aim 3

To identify if pre-treatment functional connectivity of the DLPFC cognitive control network, involving interactions with the sgACC and regions of the attention and default mode networks, and behavioral performance, along with early change in connectivity and behavior, are predictive biomarkers of clinical outcome. Our hypothesis is that baseline connectivity and behavior, and early and later changes in these measures will predict who at post-treatment have the greatest change in symptom severity, suicidality, and quality of life.

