### Data analysis plan

We will pursue a stepwise analysis plan that starts with a focus on our a priori regions of interest and builds to a model based on machine-learning of these regions, and then an exploratory phase, as follows:

For *Aim 1*, we will quantify functional connectivity in the resting and task conditions by computing correlation coefficients between the a priori regions of interest and converting these coefficients to Fisher Z scores. In task-evoked conditions we will also use gPPI to quantify connectivity incorporating the task contrast. Multivariate linear mixed models will be used to test the hypothesis that extent of connectivity is a response biomarker determining extent of post-treatment change in both connectivity and in clinical measures after 1 Week of treatment and Post-treatment (within-subjects). We will include both binary between-subjects and continuous moderators to assess whether veterans with intact pre-treatment connectivity show connectivity change after early sessions whereas veterans with impaired pre-treatment connectivity show change after completion of sessions. Correlational analyses will be used to test whether the extent of early change is proportional to the extent of baseline connectivity impairment.

For *Aim 2*, we will use the connectivity values established under Aim 1. Linear mixed models, with behavioral measures included as dependent variables, will be employed to test the hypotheses that extent of connectivity relates to extent of behavioral performance and that change in connectivity predicts change in behavioral performance (within subjects). We will include binary and continuous moderators to test if these relationships differ as a function of degree of baseline connectivity dysfunction after 1 Week and after Post-treatment sessions.

For *Aim 3*, we will again use the connectivity values established under Aim 1. Linear mixed models, with symptom, function, and suicidality measures included as dependent variables, will be employed to test the hypotheses that extent of baseline connectivity predicts severity of symptoms, functional disability and suicidality and that change in connectivity predicts changes in symptoms, function, and suicidality (within subjects). We will include binary and continuous moderators to test if these relationships differ as a function of degree of baseline connectivity dysfunction for after the 1 Week and Post-treatment sessions.

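### Aim 1 gives Baseline as its only stated reference point for change, so later change as written includes early change and the 1 Week-to-Post-treatment interval is never named

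*Protocol article*

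**What the plan says.** In the protocol article, Background, Aim 1, the broad hypothesis is that "functional connectivity will change from the pre-treatment baseline to reassessment early after commencement of TMS (targeting 5 sessions) and later", once treatment is complete. This is the only place where Aim 1 states a starting point for change, and it is Baseline for both follow-ups. The timing hypothesis comes next: "the early change will be most pronounced for patients with intact connectivity at baseline", while "later change post-treatment will be observed for those with more impaired baseline connectivity". No separate starting point is given for that later change. Aim 1 also says "we will probe whether observed changes in connectivity increase as a session-dependent function of the total number of TMS sessions".

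Under Data analysis plan, Aim 1, mixed models address "extent of post-treatment change in both connectivity and in clinical measures after 1 Week of treatment and Post-treatment (within-subjects"). Binary and continuous moderators then serve to examine this pattern: "veterans with intact pre-treatment connectivity show connectivity change after early sessions whereas veterans with impaired pre-treatment connectivity show change after completion of sessions". The interval from 1 Week to Post-treatment is not named in either section.

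Power calculation describes a within-subjects linear model with session as a repeated measure, extent of baseline connectivity dysfunction as a moderator, a correlation of 0.5 between sessions, a two-sided alpha of 0.05, and at least 98 veterans.

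**The concern.** The timing hypothesis is about when change happens: early in veterans with intact connectivity, late in those with impaired connectivity. Only the interval between the 1 Week and Post-treatment scans holds late change alone. If late change is counted from Baseline, as the broad hypothesis counts it, a Post-treatment comparison of intact with impaired veterans mixes the two periods. Its size and sign then depend on whether intact veterans keep their early gain and on how the groups' total changes compare, and the hypothesis addresses neither.

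There is a second difficulty. The moderator is baseline connectivity, and the Baseline scan is also subtracted in the outcome. This produces an association between the two even when there is no moderation.

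The late half of Aim 1's main moderation hypothesis is at stake, and with it the added value of the middle scan, which the Discussion presents as a strength of the design.

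**Working it through.** **Inputs.** N = 98, visit correlation 0.5 and two-sided alpha 0.05 come from Power calculation. A common SD of 1, equal correlation between all pairs of visits, a 49/49 split and the mean profiles are assumptions. The article gives no power for the moderation test, so there is no planned figure to reproduce. N = 98 is taken as given, and the point does not depend on how it was reached. Write B, W and P for Baseline, 1 Week and Post-treatment.

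**1. Identity.** P - B = (W - B) + (P - W). A late change counted from Baseline therefore contains the early change.

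**2. Moderation with a group label independent of scan error.** Each simple difference has variance 2(1 - 0.5) = 1. The two-group t test has 96 degrees of freedom and noncentrality (group difference) x sqrt(49/2) = 4.95 x difference.

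Take intact veterans at 0, D, D and impaired veterans at 0, 0, D.
- P - B: the group difference is D - D = 0, so the test rejects 5% of the time at any D.
- P - W: the group difference is D - 0 = D. Noncentrality is 1.24, 2.47 and 3.71 for D = 0.25, 0.5 and 0.75, giving power 0.23, 0.69 and 0.96 (a simulation gave 0.95 for the last).

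**3. Other profiles.** The table takes intact early change as 0.5 SD and impaired early change as 0. Differences are impaired minus intact.

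| Profile | P - B difference (rejection) | P - W difference (rejection) |
|---|---|---|
| Early change kept, equal totals | 0 (5%) | 0.5 (69%) |
| Intact revert to 0 | 0.5 (69%) | 1.0 (over 99%) |
| Intact keep half | 0.25 (23%) | 0.75 (96%) |
| Impaired reach 0.75 | 0.25 (23%) | 0.75 (96%) |
| Impaired reach 1.0 | 0.5 (69%) | 1.0 (over 99%) |
| Impaired reach only 0.25 | -0.25 (23%) | 0.25 (23%) |
| Intact continue to 0.75 | -0.25 (23%) | 0.25 (23%) |

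Impaired veterans change more than intact veterans after week 1 in every row, and P - W always has that sign. P - B is zero, positive or negative. In the first row the two-degree-of-freedom moderator-by-session test has 71% power.

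**4. Moderation with measured baseline connectivity and no true moderation.** Approximate rejection rates use Fisher's z, with sqrt(98 - 3) = 9.75.
- P - B: covariance with B is 0.5 - 1 = -0.5 and variance is 1, so the correlation is -0.5. Then 0.549 x 9.75 = 5.35, and the test rejects almost always.
- P - W: covariance with B is 0.5 - 0.5 = 0, so it rejects 5%.
- Early minus late, 2W - B - P: covariance with B is 2(0.5) - 1 - 0.5 = -0.5 and variance is 3, so the correlation is -0.5/1.73 = -0.29. Then 0.297 x 9.75 = 2.90, and it rejects about 83%.

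In general, cov(B, P - W) is the Baseline-Post correlation minus the Baseline-1 Week correlation. If the first were 0.4 and the other two stayed at 0.5, P - W would correlate -0.1 with B: not zero, but far from -0.5.

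**The case against.** The strongest reply is that the plan never commits the timing hypothesis to a Baseline-to-Post comparison. The Baseline wording belongs to the broad hypothesis. The later change expected in impaired veterans has no stated reference point, and Aim 1 also asks whether "early changes in circuit connectivity are necessary, if not sufficient, for subsequent circuit and clinical changes observed post-TMS", which fits a 1 Week-to-Post reading. A three-session mixed model with a moderator can estimate that contrast, and contrast coding is often left to an analysis plan that is not shown here. All of this stands, and it limits the point to an undefined term. It does not remove the point, because the only reference point the article states is one that does not isolate late change.

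Three stronger readings are tempting, and the documents do not support them.

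- A reader might infer that the plan's own hypothesis predicts no moderation at Post-treatment. That needs early change kept, no further gain in intact veterans and equal final totals. The article states none of these, and calls early change most pronounced in the intact, not absent in the impaired. Other profiles give differences from -0.25 to +0.5 SD.
- A reader might infer that the late half cannot be confirmed when true, or would pass when false. The planned model can test it, and if impaired veterans changed wholly in week 1, the 1 Week result would show it and contradict the paired pattern.
- A reader might infer that the session-dependence question would mistake a plateau for continued change. An omnibus three-visit test would reject in 72% of trials with a plateau at 0.25 SD, but the article does not assign that test to this question. Asking whether changes increase with sessions can already mean Post-treatment minus 1 Week.

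**Conclusion.** The point holds as a definition that should be fixed. As written, later change has Baseline as its only stated reference point, so it includes early change, and the interval that isolates it is unnamed.

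The cost of the Baseline reading depends on the true pattern. In the kept-and-equal pattern, the Baseline-to-Post test has no power beyond its 5% error rate, against 0.23 to 0.96 for Post-treatment minus 1 Week. In other patterns it may have either sign. These figures assume an error-free 49/49 label, so they do not describe a test that uses measured baseline connectivity. For that test the shared Baseline scan dominates: Baseline-to-Post change correlates about -0.5 with the moderator when nothing is moderated, while Post-treatment minus 1 Week correlates 0 if all visit correlations are equal.

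The planned scans and model are sufficient to test the late half of the hypothesis.

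**What to change.** In Background (Aim 1) and Data analysis plan (Aim 1):

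- Define early change as 1 Week minus Baseline and late change as Post-treatment minus 1 Week.
- Test the late half of the timing hypothesis as baseline connectivity by (Post-treatment minus 1 Week), as a named contrast in the planned three-session mixed model.
- Report Baseline-to-Post change as overall change only.
- Conclude that change keeps increasing with sessions only from the Post-treatment minus 1 Week contrast.
- Do not replace these with a single early-minus-late contrast when measured baseline connectivity is the moderator, unless the shared error of the Baseline scan is handled. That contrast reuses the Baseline scan and rejects about 83% of the time with no true moderation.

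The early contrast also subtracts the Baseline scan and has the same -0.5 correlation with the moderator. This redefinition cures the late half only.

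The cost is wording; no scan or visit is added. The downside is that a veteran without a usable 1 Week scan adds little to the late contrast, and Table 2 gives that visit the tightest limit (unusable beyond 96 hours, against 14 days for the other two).

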### Interactions, covariates and cross-validation

Under each of these aims, we will evaluate if the interaction of the DLPFC-anchored cognitive control network with resting attention and default mode networks, and the sgACC, further moderates these relationships. In each analysis, we will model sex, medication, medication change, comorbidity, substance use, and premorbid function as covariates. We will employ cross-validation techniques, as used in our prior pharmacotherapy and imaging trials [14, 73, 74], to assess the rigor of our inferences.

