#### Implementation of longitudinal design

We will be obtaining fMRI scans at three time points during the course of TMS (baseline, after 1 Week and Post-treatment), while other TMS neuroimaging studies have obtained images at only one (Baseline) or two time points (Baseline and Post-treatment). Our approach will allow us, for the first time, to investigate whether change in functional connectivity of particular neural circuits in response to TMS may serve as an early biomarker (i.e., after only a few TMS sessions) of the subsequent effect of TMS. This information could enable clinicians to discontinue an intensive therapy for certain patients early in the TMS course, allowing the right treatment to be identified more quickly, aborting unnecessary side effects, and lowering the risk of patients disengaging from care due to frustration.

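### Aim 3 counts change measured at Post-treatment as a predictor of an outcome taken at the same visit, and its early-biomarker claim is not separated from symptom change already present at 1 Week

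*Protocol article*

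**What the plan says.** Three statements of what is meant to predict what do not agree.

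- The opening sentence of Aim 3 names pre-treatment connectivity and behavior, "along with early change in connectivity and behavior, are predictive biomarkers of clinical outcome".
- The abstract asks "whether baseline and early change in neural target and cognitive behavioral performance predict subsequent symptom severity".
- The Aim 3 hypothesis adds later change: "early and later changes in these measures will predict who at post-treatment have the greatest change in symptom severity, suicidality, and quality of life". Aim 1 places the later reassessment "later, post- completion of treatment (targeting 30 sessions").

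The Aim 3 paragraph of the data analysis plan uses linear mixed models with the clinical measures as dependent variables. It tests "that change in connectivity predicts changes in symptoms, function, and suicidality (within subjects"), without saying which interval of connectivity change is related to which interval of clinical change.

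Under Interactions, covariates and cross-validation, the plan says of each analysis that "we will model sex, medication, medication change, comorbidity, substance use, and premorbid function as covariates". No clinical score is in that list.

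Table 4 schedules functional MRI, QIDS-SR, VR-36 and C-SSRS at Baseline, 1 Week and Post-treatment alike. The Strengths section (Implementation of longitudinal design) says that connectivity change "may serve as an early biomarker (i.e., after only a few TMS sessions) of the subsequent effect of TMS", and names decisions about continuing treatment early in the course as the use.

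**The concern.** Two separate things are at stake.

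First, a change that ends at the outcome visit cannot forecast the outcome. If it is analyzed under the heading of prediction, an ordinary same-time correlation between brain change and symptom change may be reported as a predictive biomarker.

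Second, early connectivity change does come before the Post-treatment outcome, but it is measured at the same visit as the 1-week symptom scores. Clinical change from Baseline to Post-treatment includes the part that has already happened by 1 Week. A scan that only mirrors how much better the veteran already feels at that visit will correlate with total change, although it says nothing about what follows. The Strengths section makes its claim about what follows. A short self-report score, already collected at that visit, would carry the same information.

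**Working it through.** **Timing, from the documents**

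| Predictor in the Aim 3 hypothesis | Last measured at | Outcome completed at | Lead time |
|---|---|---|---|
| Baseline connectivity and behavior | Baseline | Post-treatment | whole course |
| Early change | 1 Week | Post-treatment | 1 Week to Post-treatment |
| Later change | Post-treatment | Post-treatment | none |

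The third row is what the opening sentence of Aim 3 and the abstract leave out.

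**Why total change does not isolate the subsequent effect**

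Let Q0, Q1 and Q2 be a symptom score at Baseline, 1 Week and Post-treatment. Then Q2 − Q0 = (Q1 − Q0) + (Q2 − Q1). The first bracket is already known when early connectivity change C is measured.

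**Illustration**

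The plan gives no correlations and no power figure for this question, so the following are assumptions: equal SDs; adjacent-visit correlation a of 0.6 to 0.8; Q2 depends on the past only through Q1; C correlates g = 0.2 to 0.4 with Q1 − Q0 and carries nothing further. The size is n = 100, the plan's target, with two-sided alpha 0.05.

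Under these assumptions:

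- Var(Q1 − Q0) = 2(1 − a)
- Var(Q2 − Q0) = 2(1 − a²)
- Cov(Q1 − Q0, Q2 − Q0) = a − a − a² + 1 = 1 − a²
- Corr(Q1 − Q0, Q2 − Q0) = √(1 + a)/2, which is 0.632, 0.652 and 0.671 for a = 0.6, 0.7 and 0.8
- Corr(C, Q2 − Q0) = g × √(1 + a)/2

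For a = 0.7 and g = 0.3 this is 0.3 × 0.652 = 0.196. By Fisher z, atanh(0.196) × √97 = 1.96, which gives a probability of significance of about 0.50. Simulation (6,000 trials per setting) gives 0.503.

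Simulated proportion of trials in which C is significant for Q2 − Q0:

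| a | g | no symptom score | Baseline score | Baseline and 1-week scores |
|---|---|---|---|---|
| 0.6 | 0.2 | 0.234 | 0.144 | 0.052 |
| 0.6 | 0.4 | 0.708 | 0.446 | 0.050 |
| 0.7 | 0.3 | 0.503 | 0.361 | 0.047 |
| 0.8 | 0.2 | 0.254 | 0.206 | 0.048 |
| 0.8 | 0.4 | 0.778 | 0.664 | 0.047 |

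Over the full grid with g from 0.2 to 0.4 the ranges are 23–78%, 14–66% and 4.7–5.5%. At g = 0 all three are about 5%.

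**Later change**

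A purely concurrent correlation of 0.2, 0.3 or 0.4 between later connectivity change and clinical change would be significant at n = 100 with probability 0.52, 0.86 or 0.99 (Fisher z), with no lead time at all.

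**The case against.** **The rates are power, not error.** In the illustration C truly correlates with total change, so rejecting the null of no association is correct. It misleads only if the result is read as information beyond the 1-week score. This stands. A reader might infer that the planned test has a false-positive rate of 23% to 78%. The documents do not support that, because the correlations are assumed and the plan does not specify this exact test.

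**The mixed model already uses the earlier scores.** With clinical measures as dependent variables within subjects, Baseline and 1-week values would normally enter as outcome rows, so their absence from a covariate list is not surprising. This stands as far as it goes: it would be wrong to say that the plan ignores them. But an outcome row does not condition the early-change effect on 1-week symptoms, and in the illustration adjustment for Baseline alone is not enough.

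**1-week symptoms may lie on the pathway.** The premise is that stimulation acts through cognitive control circuits, and Aim 1 asks whether early circuit change is necessary for later clinical change. Conditioning on the 1-week score could remove part of a real mediated effect. This stands, and it rules out replacing the unadjusted model.

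**Added value is not the stated aim.** The definition of a predictive biomarker that the article adopts does not require superiority over a questionnaire. True of Aim 3, but the Strengths section speaks of the subsequent effect, and total change does not test that.

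**Later change is a slip of wording.** Plausible, given the abstract and the opening of Aim 3. A reader might infer that Post-treatment change is meant to guide prospective decisions; nothing in the article says so. The hypothesis as written still includes it, and the analysis paragraph does not exclude it.

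**An analysis plan not shown may add the terms.** Possible, and the covariate list is not said to be exhaustive. The conflict among the three statements of the aim is in this document all the same. The planned cross-validation cures neither problem, because a concurrent or symptom-tracking association also cross-validates.

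**Conclusion.** The concern holds on two points. The Aim 3 hypothesis calls a same-visit association prediction, against the article's own narrower statements, and no lag is stated. The claim of an early marker of the subsequent effect is not separated from symptom change already present at 1 Week. The first point rests on the text and visit schedule alone. The second rests on the text for its direction; its size depends on how strongly early connectivity change moves with early symptom change, which the documents do not give, and it vanishes if that correlation is zero. The plan should be changed here, because the wording decides what Aim 3 can conclude. The design and data collection are not at fault.

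**What to change.** - Reserve the word predict for baseline and 1-week measures, in line with the abstract and the opening sentence of Aim 3. Report later change as a concurrent association.
- State the interval of predictor change and of outcome change for each Aim 3 model.
- Model the Post-treatment score adjusted for the Baseline score.
- For early-change predictors, report beside that model, not in its place, a second model that also adjusts for the 1-week score. Base any claim of early-biomarker value for subsequent change on this added-value model.

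The cost is analysis wording only, since all scores are scheduled at all three visits. The early-biomarker claim becomes harder to reach, and adjustment for the 1-week score may remove part of a mediated effect. That is the reason for reporting both models.
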